### Interim analyses {21b}

*Timing of interim analyses*: Interim analyses will be conducted at pre-defined time points during the trial. These points will be carefully selected to ensure meaningful insights while minimizing the risk of bias. Interim analyses are planned to occur after approximately 50% of participants have completed the trial and before the final analysis.*Statistical methods*: Interim analyses will be performed using appropriate statistical methods to ensure robustness and validity. An independent statistical analyst not involved in the day-to-day conduct of the trial will perform the analyses. To maintain statistical integrity, these analyses will utilize adjusted significance thresholds to account for multiplicity issues arising from multiple looks at the data.
*Stopping guidelines*: Well-defined stopping guidelines will be established in advance to guide decision-making based on interim results. Stopping criteria will be based on pre-specified thresholds for safety or efficacy, as determined through statistical methods such as Bayesian or frequentist approaches. The researchers (CX and [name]) will review the interim findings and make recommendations regarding study continuation or modification.

### Methods for additional analyses (e.g., subgroup analyses) {20b}

We plan to classify the severity of each group of patients into severe pain and moderate pain according to the NRS and analyze whether there are differences in changes between them.

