**Methods:**

In this trial, we will randomly assign 104 adults with chronic low back pain (CLBP) to either an intervention or control group, with 52 participants in each group. Both interventions will consist of three weekly 0.5-h sessions of core stability exercise (CSE). The intervention group will engage in home rehabilitation training utilizing key identification technology for movement, while the control group will perform supervised exercises in a hospital setting. Outcome assessments will be conducted at 4 weeks and 16 weeks after randomization. The primary outcome measure will be the change in pain intensity based on numeric rating scale (NRS scores) from baseline to 4 weeks. Secondary outcomes will include changes in physical function (measured by the Oswestry Disability Index (ODI)) and lumbar spine mobility as well as activity participation and treatment satisfaction.

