### Eligibility criteria {10}

Inclusion criteria(1) Age between 18 and 60 years.(2) Duration of low back pain of at least 12 weeks.(3) Strong willingness to participate in the study and signed informed consent.

Exclusion criteria(1) Presence of potential “red flag signs” (e.g., unilateral leg pain and numbness consistent with nerve distribution, intermittent claudication, unexplained sudden weight loss, nocturnal lumbar pain, traumatic lumbago).(2) NRS score less than 4 points.(3) Regular engagement in core stability training in the past 4 weeks.(4) Inability to independently complete the Chinese electronic questionnaire.

Exit criteria(1) Withdrawal due to sudden personal reasons.(2) Withdrawal due to apparent loss of interest in participation.(3) Failure to complete the prescribed treatment tasks as required and requesting withdrawal due to unexcused absence.

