#### Outcomes {12}

### Primary outcome

The primary outcome is the mean pain intensity over the previous week assessed using an 11-point numeric rating scale (NRS;0 = no pain, 10 = unbearable pain) at 16 weeks after randomization. A higher score indicates higher pain intensity [25]. The between-group minimal clinically important difference (MCID) is 1.0 point on the NRS scale [26]. The within-group MCID is a 30% change from baseline [27].

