### Sample size {14}

With a non-inferiority design, the intervention group and control group had a 1:1 ratio of participants. In March 2023, we conducted a pilot study in the outpatient department of the First Affiliated Hospital of Sun Yat-sen University and collected a total of 21 subjects, including 15 in the intervention group and 6 in the control group, for a 4-week intervention. They were followed up 3 months later. The result yielded mean decreases of − 1.6 (SD = 2.0) for the intervention group and − 1.9 (SD = 1.9) for the control group on the NRS. With a significance level (*α*) of 0.05 and a power (1-*β*) of 0.9, considering a non-inferiority margin of − 1 and a difference (*δ*) of 0.3 in NRS decrease between the intervention and control groups, the PASS software (version 21) estimated that each group required 41 participants. Assuming a dropout rate of 20%, a total of at least 102 participants were needed for both groups.

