## Statistical methods

### Statistical methods for primary and secondary outcomes {20a}

Statistical analysis was conducted according to intention-to-treat (ITT). The chi-square test was used to analyze categorical variables when comparing baseline demographic and clinical characteristics; For continuous variables, we first performed exploratory data analysis and Shapiro–Wilk tests to determine the normality of our data distribution, using independent *t* tests when the results conform to a normal curve and non-parametric rank sum tests when they do not.

To analyze the data, we will employ repeated measures analysis of variance (RM-ANOVA) as the statistical method. Our primary interest lies in comparing the changes over time between the intervention and control groups at baseline, 4 weeks, and 16 weeks. We will utilize repeated measures ANOVA to examine the main effects between the two groups while considering the factors of time and group. As part of the analysis, multiple comparisons will be performed, including comparisons between baseline and 4 weeks, baseline and 16 weeks, and 4 weeks and 16 weeks. These comparisons will help identify significant differences across different time points. To assess statistical significance, appropriate statistical indicators such as *F*-values and *p*-values will be utilized. In case of significant differences, post hoc multiple comparison analyses will be conducted to determine specific time points of significance. Finally, descriptive statistics and appropriate graphical representations will be employed to illustrate the overall trends and changes in the data. Statistical analyses were done using the SPSS software for Windows, version 23.

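### As most naturally read, the severity subgroup analysis compares change in severe with change in moderate patients; regression to the mean biases that contrast, and it does not test whether the home-versus-hospital difference varies with severity

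*Protocol article*

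**What the plan says.** The subgroup plan is a single sentence in the protocol article, under Methods for additional analyses {20b}. Its first half will "classify the severity of each group of patients into severe pain and moderate pain according to the NRS". Its second half gives the comparison to be made on those classes, which is to "analyze whether there are differences in changes between them". It gives neither a cut-point nor the time at which severity is classed.

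Three other places bear on it:

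- Eligibility criteria {10} excludes patients with "NRS score less than 4 points", so entry is already truncated on this scale.
- Primary outcome: "The primary outcome is the mean pain intensity over the previous week assessed using an 11-point numeric rating scale". The scale that forms the classes is also the one on which change is measured.
- Statistical methods {20a} states "Our primary interest lies in comparing the changes over time between the intervention and control groups" and plans a repeated-measures ANOVA to "examine the main effects between the two groups while considering the factors of time and group". Severity is not a factor, and no treatment-by-severity term appears there or elsewhere.

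**The concern.** A subgroup analysis in a randomised comparison of home and hospital training should ask whether the home-minus-hospital difference depends on severity. The sentence, on its nearest reading, asks whether severe patients change more than moderate ones. That is a prognostic question and says nothing about the treatment contrast.

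The comparison is also biased. A patient recorded as severe at baseline is there partly because of a high measurement that day, and on re-measurement that part is lost. The severe class therefore falls further on average under any treatment. Followed as written, the analysis could be reported as showing that severe patients benefit more when no such effect exists. The artefact can be large on this trial's own scale, since the Primary outcome section sets the between-group MCID at 1.0 point.

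**Working it through.** The plan gives no figure for this analysis, so there is none to reproduce. The check is how large the artefact is when there is nothing to find.

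**Inputs from the protocol article.** 104 patients randomised 1:1 (Abstract, Methods); entry at NRS 4 or more (Eligibility criteria); pilot SDs of change of 2.0 and 1.9, and 20% dropout (Sample size).

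**Assumptions, not in the document.** Severity classed at baseline; severe means NRS 7 or more; baseline mean 5.5 and SD 1.8 before the entry cut; the same average true fall of 1.75 points in both classes and both arms; test-retest correlation ρ from 0.6 to 0.9.

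**Step 1: size of the artefact.** With no true difference, the expected extra fall in severe patients is (1 − ρ) × (mean baseline in severe − mean baseline in moderate). Whole-number scores of 7 or more, and of 4 to 6, correspond to underlying values above 6.5, and from 3.5 to 6.5.

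- Severe mean: 5.5 + 1.8 × 0.342/0.289 = 7.63.
- Moderate mean: 5.5 + 1.8 × (0.215 − 0.342)/0.577 = 5.10.
- Gap: about 2.52. Share severe among entrants: 0.289/0.867 = 33%.

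Simulation of the recorded whole-number scale gives slightly more, because rounding the baseline widens the recorded gap by about 0.06:

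| ρ | (1 − ρ) × 2.52 | Simulated extra fall |
|---|---|---|
| 0.6 | 1.01 | 1.07 |
| 0.7 | 0.76 | 0.81 |
| 0.8 | 0.50 | 0.56 |
| 0.9 | 0.25 | 0.31 |

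Other source populations (mean 5, SD 1.8; mean 5.5, SD 1.5) give 0.97 to 1.06 points at ρ = 0.6 and 0.30 to 0.32 at ρ = 0.9.

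**Step 2: chance of a falsely significant result (two-sided 5%).** If every patient has the same true fall, the SD of change among entrants is only 1.59, 1.41, 1.18 and 0.89 at the four correlations, below the pilot's 1.9 to 2.0. A second set of runs therefore adds person-to-person variation in true change, unrelated to baseline, until the SD reaches 1.95. The extra fall is then about 1.09, 0.85, 0.60 and 0.37.

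| ρ | Same response, n = 104 | SD 1.95, n = 104 | SD 1.95, n = 83 (20% dropout) | SD 1.95, one arm of 52 |
|---|---|---|---|---|
| 0.6 | 92% | about 80% | 70% | 50% |
| 0.7 | 83% | about 56% | 47% | 32% |
| 0.8 | 64% | about 33% | 27% | 18% |
| 0.9 | 38% | about 15% | 13% | 10% |

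Hand check at ρ = 0.6 and SD 1.95, with 34.7 severe and 69.3 moderate patients:

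- Within-class SD: √(1.95² − 0.333 × 0.667 × 1.09²) = 1.88.
- Standard error: 1.88 × √(1/34.7 + 1/69.3) = 0.391.
- z = 1.09/0.391 = 2.79, so the rate is Φ(2.79 − 1.96) = 80%.

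**Step 3: the interaction instead.** Randomisation gives both arms the same regression to the mean within a class, so it cancels from the treatment difference. In simulations with the same response in everyone (N = 104, ρ 0.5 to 0.9, the two other source populations), the treatment-by-severity interaction averaged −0.03 to +0.02 points and rejected in 4.0% to 6.1% of trials. Its standard error relative to the overall treatment difference is 1/√(f(1 − f)), where f is the share severe: 2.0 at f = 0.5 and 2.2 at f = 0.3.

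**The case against.** **The sentence is ambiguous.** *Them* could mean the two arms within each severity class, and the main analysis section, which compares the arms, lends that some support. This stands. On that reading the regression artefact largely cancels and the sizes above do not apply. What remains is a pair of separate within-class tests. Finding one significant and the other not does not show that the treatment difference varies with severity, so the sentence still needs rewording.

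**Detail may sit in a full protocol or SAP.** The cut-point, the time of classification and the model form may well be there, and their absence from an article is not the point. The article does state a contrast, and it is the form of that contrast that is at issue.

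**The error rates depend on assumptions.** This also stands. A reader might infer that the analysis is bound to give a false significant result. The documents do not support that: they give no correlation, baseline distribution or cut-point. At the pilot's SD of change, with the excess attributed to varied response, a false positive is the less likely outcome at correlations of 0.8 and 0.9. In the other direction, if the pilot's SD reflects measurement noise, the correlation would be nearer 0.4 and the artefact about 1.6 points.

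**It is only an additional analysis.** Correct. A reader might infer that the non-inferiority conclusion is at risk, but nothing in the subgroup sentence feeds into it. The objectives also do not promise a non-inferiority statement for severe patients, and an interaction estimate from 104 patients could barely support one.

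**Conclusion.** The concern holds in this form. On its most natural reading, and with severity classed at baseline, the planned contrast is biased towards a larger fall in severe patients and does not address whether the treatment difference varies with severity. The bias is about 0.3 to 1.1 NRS points for correlations of 0.9 to 0.6, so at the low end of that range it is about as large as the plan's MCID. The false-positive rate in 104 patients exceeds 5% throughout: about 38% to 92% with a homogeneous response, about 15% to 80% at the pilot's SD. The direction of the bias is secure on this reading; its size, and significance in any one trial, are not. On the alternative reading the bias largely disappears, but the treatment difference is still not compared across severity. The point is worth correcting but does not touch the primary conclusion.

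**What to change.** Reword the sentence in the subgroup section to:

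- estimate the treatment-by-baseline-NRS interaction in a model of follow-up NRS adjusted for baseline NRS, with baseline either continuous or in the two classes, and any classes fixed at baseline by a stated cut-point;
- report the home-minus-hospital difference with its confidence interval in each severity class;
- label the analysis exploratory.

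A severe-versus-moderate comparison of change, if shown at all, should be descriptive and not read as a treatment effect.

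The cost is a sentence or two of wording and no new data. The drawback is precision: the interaction has a standard error about twice that of the overall difference, so the result will probably be inconclusive and should be presented as such.

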### Methods in analysis to handle protocol non-adherence and any statistical methods to handle missing data {20c}

For continuous outcomes, such as numeric rating scale (NRS) scores, a multiple imputation approach will be utilized to address missing data. Imputation will be performed using covariates and auxiliary variables that are pertinent to the analysis. The imputed datasets will be subject to analysis, and the outcomes will be aggregated to ensure unbiased estimations and reliable inferences. To enhance the robustness of findings in the presence of missing data, sensitivity analyses will be conducted. These analyses will evaluate the resilience of results to diverse assumptions concerning missing data. Variation in imputation methodologies or mechanisms will be explored to assess their potential impact on the derived conclusions. By incorporating sensitivity analyses, the credibility of outcomes will be fortified across a spectrum of scenarios.

### Plans to give access to the full protocol participant-level data and statistical code {31c}

In accordance with the data sharing statement, we commit to providing a fully deidentified dataset to a suitable data repository for the purpose of sharing. This will be done within 3 years following the completion of the 1-year post-randomization interviews.

#### Oversight and monitoring

### Composition of the coordinating center and trial steering committee {5d}

The researchers and all aspects of the study will be supervised by the ethics committee of the First Affiliated Hospital of Sun Yat-sen University, who will ensure that the study adheres to ethical principles and protects the patient’s health and dignity.

### Composition of the data monitoring committee, its role and reporting structure {21a}

A data monitoring committee (DMC) is not needed, because our trial is short duration and with known minimal risks. But the researchers (CX and [name]) will regularly analyze the data to make adjustments.

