#### Assignment of interventions: blinding

### Who will be blinded {17a}

It is not possible to blind the participants and the researcher due to the nature of the experiment’s design.

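### Regular data analysis by unblinded researchers, with no limit on content or number of looks, conflicts with the plan's controlled interim analysis

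*Protocol article*

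**What the plan says.** Two sections of the protocol article govern looks at the data during the trial.

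- **Interim analyses {21b}.** "Interim analyses will be conducted at pre-defined time points during the trial". The only time point named is in the statement that "Interim analyses are planned to occur after approximately 50% of participants have completed the trial and before the final analysis". On who does the work: "An independent statistical analyst not involved in the day-to-day conduct of the trial will perform the analyses". On error control: "these analyses will utilize adjusted significance thresholds to account for multiplicity issues arising from multiple looks at the data". Stopping guidelines for safety or efficacy are to be set in advance. The trial researchers then "will review the interim findings and make recommendations regarding study continuation or modification".
- **Composition of the data monitoring committee {21a}.** "A data monitoring committee (DMC) is not needed, because our trial is short duration and with known minimal risks". The next sentence says that the researchers "will regularly analyze the data to make adjustments".

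On blinding, Who will be blinded {17a} states: "It is not possible to blind the participants and the researcher". The section on unblinding {17b} adds that no blinding was used. Only the statistical analyst is described as blinded, in the data collection section {18a}. The primary outcome is a pain score reported by the participant.

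**The concern.** The sentence in {21a} stands where a monitoring committee would normally be described, and it hands recurring analysis to people who know the allocation. It sets no schedule, no threshold, no restriction to data pooled over arms and no boundary on the adjustments. Two things are at stake.

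1. **Error control.** The thresholds promised in {21b} protect the type I error only against the looks they were calculated for. Further comparative looks outside that scheme are not covered.
2. **Conduct.** The trial is open-label and the outcome self-reported. The article also allows programmes to be modified {11b} and adherence to be encouraged through tailored plans and feedback {11c}. Researchers who know which arm is ahead have practical ways to influence delivery or retention, even if no test is ever run.

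**Working it through.** **1. The two sections side by side**

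| Feature | Interim analyses {21b} | Monitoring section {21a} |
|---|---|---|
| Timing | Pre-defined; about 50% completion named | Regular; no schedule |
| Who analyses | Independent analyst outside daily conduct | The trial researchers |
| Threshold | Adjusted for multiple looks | None mentioned |
| Scope | Safety or efficacy thresholds | Not limited |
| Consequence | Recommendation on continuing or modifying | Adjustments, not limited |

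They differ in every row. The researchers who review the interim findings appear to be the same people in both sections, although part of the identification is removed from the text.

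**2. The plan's own figure**

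The article gives no number of looks and no overall error rate. The figure that can be checked is 41 per group (Sample size {14}). The inputs are alpha 0.05, power 0.9, margin 1, difference 0.3, and SD 2.0 and 1.9. The fixed-sample formula is

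n = 2 × SD² × (z for 1−α + z for 1−β)² / (distance to margin)².

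With one-sided 0.05, SD 2.0 and a distance of 1.3:

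n = 2 × 4 × (1.645 + 1.282)² / 1.69 = 8 × 8.567 / 1.69 = 40.6, so 41.

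One-sided 0.025 gives 48 to 50 and does not match. The stated size is therefore consistent with a single final test at one-sided 0.05. (The distance of 1.3 treats the 0.3 as favouring the intervention. Whether that is justified is a separate matter.)

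**3. Error rate if the regular looks are comparative**

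Assume K equally spaced looks, the last being the final analysis, with a claim possible at each and no adjustment. The statistic at look k is Z(k) = S(k)/√k, where S(k) is the sum of k independent standard normal increments. The error is the probability that any Z(k) exceeds the nominal critical value when the true difference lies at the margin. Simulation with 1,000,000 runs gives:

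| Looks | Nominal one-sided 0.05 (1.645) | Nominal one-sided 0.025 (1.96) |
|---|---|---|
| 1 | 0.050 | 0.025 |
| 2 | 0.080 | 0.042 |
| 3 | 0.101 | 0.054 |
| 5 | 0.130 | 0.072 |
| 10 | 0.172 | 0.097 |

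**4. Effect on a properly adjusted interim**

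The article names no boundary, so two common ones are assumed, with looks at 50% and 100%. A Pocock-type boundary (1.875 at both looks) and an O'Brien-Fleming-type boundary (2.373, then 1.678) each hold one-sided 0.050. Now add two looks, at 25% and 75%:

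- Extra looks at 1.645: 0.099 (Pocock-type) and 0.101 (O'Brien-Fleming-type).
- Extra looks at 1.875, added to the Pocock-type design: 0.075.

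Two uncontrolled looks are enough to double the error of a correct design.

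**5. Sample-size cost of an adjusted interim**

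Using the O'Brien-Fleming-type final value, the inflation is about

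((1.678 + 1.282) / (1.645 + 1.282))² = (2.960 / 2.927)² = 1.02,

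and 41 × 1.02 is about 42, or one participant per group.

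**The case against.** The strongest defence is that the sentence in {21a} never says the analyses are by arm, test efficacy or can support a conclusion. It follows a statement that risks are minimal. Elsewhere the article describes harmless monitoring: modifying a participant's programme {11b}, tracking progress {11c} and auditing every 4 weeks {23}. If that is all that is meant, type I error is unaffected.

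This stands as far as the size of any inflation goes: the error rates above are conditional. It does not remove the conflict. The sentence carries no such limit. The audit section already covers adherence, safety and data quality, so the sentence reads as something additional. If only housekeeping is meant, the authors lose nothing by saying so.

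Three further inferences are tempting, and the article does not support them.

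- **That exactly one interim analysis is planned.** Section {21b} uses the plural and refers to multiple looks. It merely names one time point.
- **That these researchers treat or assess participants.** A therapist instructs the control group, and outcomes are collected by electronic questionnaire. The article shows only that the researchers are unblinded and act on findings.
- **That the sample size is materially too small because it makes no allowance for interim testing.** Under an O'Brien-Fleming-type boundary the allowance is about one participant per group. The choice of boundary may properly sit in the full protocol or analysis plan.

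**Conclusion.** The point holds as a contradiction that should be fixed. Section {21a} permits an unlimited number of analyses by unblinded researchers, with adjustments to follow. Section {21b} requires pre-defined, independent and threshold-adjusted looks. Following {21a} as written would defeat the control promised in {21b}.

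A reader might infer that this trial's error rate is 8% to 13%. The article does not support that. Those figures assume by-arm outcome tests, a claim possible at every look, unadjusted one-sided 0.05, equal spacing, and 2 to 5 looks including the final one. None of these is stated. In particular, the 2-look figure does not describe the planned interim plus final analysis, for which adjusted thresholds are promised.

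The risk to conduct needs fewer assumptions: only that the researchers see results by arm. Nothing in {21a} prevents this, and {21b} routes the interim findings to the researchers. The size of that effect cannot be calculated from the article.

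**What to change.** 1. In {21a}, delete the sentence on regular analysis, or restrict it to listings pooled over arms that cover recruitment, data quality, adherence and safety.
2. In {21b}, state that comparisons between arms occur only at the pre-defined interim, are performed by the independent analyst, and use the adjusted threshold.
3. In {21b}, keep by-arm interim results from the trial researchers. Give them only the analyst's continue-or-stop outcome against the thresholds set in advance.

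Dropping efficacy stopping is optional. With a proper two-look boundary it leaves alpha intact at almost no cost in participants, so it is a trade-off for the sponsor. If by-arm results were to go to the ethics committee instead, that role would have to be added, because {5d} gives it ethical supervision and does not mention review of comparative data.

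The cost is a wording amendment and the researchers' loss of by-arm data during the trial. Trial status describes recruitment as still to come. If that remains so, the change can be made before any outcome data exist.
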